## Abstract

**Background:**

Trials investigating neoadjuvant treatment with immune checkpoint inhibitors (ICI) in patients with melanoma have shown high clinical and pathologic response rates. Treatment with talimogene laherparepvec (T-VEC), a modified herpes simplex virus type-1 (HSV-1), is approved for patients with unresectable stage IIIB-IVM1a melanoma and has the potential to make tumors more susceptible for ICI. Combination ICI and intralesional T-VEC has already been investigated in patients with unresectable stage IIIB-IV disease, however, no data is available yet on the potential benefit of this combination therapy in neoadjuvant setting.

**Methods:**

This single center, single arm, phase II study aims to show an improved major pathologic complete response (pCR) rate, either pCR or near-pCR, up to 45% in 24 patients with resectable stage IIIB-IVM1a melanoma upon neoadjuvant combination treatment with intralesional T-VEC and systemic nivolumab (anti-PD-1 antibody). Patients will receive four courses of T-VEC up to 4 mL (first dose as seroconversion dose) and three doses of nivolumab (240 mg flatdose) every 2 weeks, followed by surgical resection in week nine. The primary endpoint of this trial is pathologic response rate. Secondary endpoints are safety, the rate of delay of surgery and event-free survival. Additionally, prognostic and predictive biomarker research and health-related quality of life evaluation will be performed.

**Discussion:**

Intralesional T-VEC has the capacity to heighten the immune response and to elicit an abscopal effect in melanoma in combination with ICI. However, the potential clinical benefit of T-VEC plus ICI in the neoadjuvant setting remains unknown. This is the first trial investigating the efficacy and safety of neoadjuvant treatment of T-VEC and nivolumab followed by surgical resection in patients with stage IIIB-IVM1a melanoma, with the potential of high pathologic response rates and acceptable toxicity.

**Trial registration:**

This trial was registered in the European Union Drug Regulating Authorities Clinical Trials Database (EudraCT- number: 2019–001911-22) and the Central Committee on Research Involving Human Subjects (NL71866.000.19) on 4th June 2020.

Secondary identifying number: NCT04330430.

## Background

The worldwide incidence of melanoma is still increasing and accounted for more than 57.000 deaths in 2020 [1]. The prognosis of patients is clearly correlated with disease stage, but since the introduction of the current standard systemic treatments comprising targeted therapies and immune checkpoint inhibitors (ICI), 5-year overall survival (OS) rates up to 50% have been reached in patients with unresectable stage IIIC-IV melanoma in clinical trials [2, 3]. For patients with high-risk stage IIIB, IIIC, IIID (AJCC 8th edition) melanoma, the prognosis is slightly better, with 5-year OS rates of 83, 69 and 32% respectively, although it must be noted that this is prior to effective adjuvant therapy becoming available [4]. Adjuvant targeted therapy or ICI has shown major improvements in relapse-free survival (RFS) in patients with resectable stage III or IV melanoma [5–8] and is currently standard of care.

Next to the currently available systemic therapies for patients with advanced melanoma, local oncolytic viral immunotherapy with talimogene laherparepvec (T-VEC) has been approved for the treatment of patients with unresectable stage IIIB-IVM1a melanoma with cutaneous, subcutaneous or nodal metastases [9]. T-VEC, a modified herpes simplex virus type-1 (HSV-1), is administered intralesionally and resulted in high and durable response rates with a mild toxicity profile, consisting mostly of fatigue and influenza-like symptoms, confirmed in real-world setting [10–12]. However, there is still a group of patients that has no (durable) benefit upon these currently approved systemic and local treatment options.

A possible way to overcome this resistance to therapy is combination of treatments. Although single agent T-VEC has already proven its efficacy, evidence is also emerging that combination of T-VEC with ICI could have an additive anti-tumor effect. This is demonstrated by two clinical trials treating patients with unresectable stage IIIB-IV melanoma with T-VEC in combination with either ipilimumab, an anti-CTLA-4 antibody, or pembrolizumab, an anti-PD-1 antibody, reaching objective response rates of 39% [13] and 62% [14] respectively. In both trials, the responses were not limited to the injected lesions, suggesting an abscopal effect of T-VEC in combination with ICI. In the phase Ib trial by Ribas et al. [14], 21 patients with unresectable stage IIIB-IV cutaneous melanoma were treated with intralesional T-VEC and systemic pembrolizumab. The majority of patients showed increases in circulating CD4^+^ and CD8^+^ T cells after T-VEC alone, with no significant further increase after pembrolizumab administration. Additionally, increases in CD8^+^ T cells, IFN-γ gene and PD-L1 protein expression were seen within the tumors of responding patients treated with T-VEC and pembrolizumab compared to baseline. These changes in the tumor microenvironment have also been observed by multiple other preclinical and clinical trials [15–17], indicating that T-VEC is able to heighten the immune response and turn an immune desolate “cold” tumor into an immunogenic “hot” tumor, making the tumor more susceptible to ICI treatment. Although the clinical benefit of the combination of T-VEC and pembrolizumab compared to single agent pembrolizumab in patients with unresectable stage IIIB-IVc was not confirmed in the recent phase III trial by Ribas et al. (2021), progression-free survival did seem to be improved in the combination treatment arm and patients with few sites of disease tended to have a better response upon treatment [18], still suggesting a heightened immune response in this patient population. In the previous trials no dose-limiting or novel adverse events (AE) were observed, indicating that combination treatment with T-VEC and ICI can be administered safely to possibly overcome tumor resistance.

Aside from the type of treatment, there is increasing evidence that the timing of the given therapies also plays a key role in the chances of a tumor response [19]. Neoadjuvant therapy, administered prior to surgery, could result in a broader tumor-specific T cell response compared to adjuvant treatment, downsizing of the tumor leading to less extensive surgery, and usage of the pathologic response for fitted (adjuvant) therapy [19, 20]. The benefit of neoadjuvant ICI has been investigated in multiple clinical trials, resulting in high pathologic complete response (pCR) rates of 25–80% [21–24]. Recently, the role of neoadjuvant T-VEC in resectable stage IIIB-IVM1a melanoma has been investigated by Dummer et al. [25] in a randomized study of single agent T-VEC followed by surgery, compared to surgery alone. This trial showed a pCR rate of 17.1% and an improved 2-year RFS and OS for the T-VEC + surgery arm (29.5% vs 16.5 and 88.9% vs 77.4% respectively).

Based on the recent data of neoadjuvant single agent nivolumab and pembrolizumab shown by Amaria et al. [23] and Huang et al. [24], with pCR rates of 25 and 20% respectively, neoadjuvant single agent T-VEC shown by Dummer et al. [25] and the abscopal effect of T-VEC in combination with ICI, we hypothesized that neoadjuvant T-VEC in combination with nivolumab can improve these pCR or pathologic near complete response (near-pCR) rates further. For this, we designed a single arm phase II trial treating patients with stage IIIB-IVM1a melanoma with resectable (sub)cutaneous satellite or in-transit metastases and/or tumor positive lymph nodes with neoadjuvant nivolumab and T-VEC (NIVEC trial). The aim of this trial is to show an improvement in pCR (or near-pCR) rate of 25% compared to the pCR rate observed by Amaria et al. [23] and Huang et al. [24], reaching a pCR rate of 45% in this patient population. In total, 24 patients will be included and evaluated for efficacy and safety. This is the first trial evaluating neoadjuvant T-VEC and ICI combination therapy and may benefit a large group of future melanoma patients.

## Methods

### Study design

The NIVEC trial is an investigator initiated, single-center, single-arm, open-label, phase II study investigating the efficacy and safety of neoadjuvant combination of T-VEC plus nivolumab in patients with resectable stage IIIB-IVM1a melanoma. Patients will be enrolled and treated at the departments of Medical and Surgical Oncology at the Netherlands Cancer Institute (NKI), Amsterdam, The Netherlands, after signing a written informed consent form. A Data and Safety Monitoring Board (DSMB) has been established to monitor the safety of the patients throughout the study.

### Objectives

#### Primary objective

The primary objective of this trial is to investigate the major pathologic complete response rate, either pCR or near-pCR, of neoadjuvant combination of T-VEC and nivolumab, in patients with resectable stage IIIB/C/D/IVM1a melanoma, with the aim to achieve a major pathologic complete response rate of 45%.

#### Secondary objectives

To investigate the rate of delays or failures (delays ≥14 days) to perform surgery;To investigate the effect of neoadjuvant combination of T-VEC and nivolumab on event-free survival (EFS);To determine the safety of neoadjuvant combination of T-VEC and nivolumab;To acquire tumor material for prognostic and predictive biomarker research, for example CD8, IFN-γ and PD-L1, as well as exploration if expansion of tumor-resident T cells can be observed within the tumor after neoadjuvant treatment.

#### Exploratory objectives

To assess radiologic response rates according to RECIST 1.1 after neoadjuvant T-VEC and nivolumab at week eight;To evaluate health-related quality of life.

### Participants

Patients of ≥18 years with treatment naïve resectable stage IIIB/C/D/IV M1a melanoma according to the American Joint Committee on Cancer (AJCC) 8th edition, a good clinical performance score of 0–1 and < 2 times elevated lactate dehydrogenase levels will be eligible for this trial. Patients must have measurable disease according to RECIST 1.1 [26] and must be a candidate for intralesional therapy with at least one injectable cutaneous, subcutaneous or nodal melanoma lesion (≥ 10 mm in longest diameter) or with multiple injectable lesions that in aggregate have a longest diameter of ≥10 mm. Patients with visceral or brain metastases, prior systemic cancer therapies or a history of other malignancies or autoimmune/infectious diseases will not be eligible. For a full overview of all in- and exclusion criteria, see Table 1.

**Table 1 Tab1:** In- and exclusion criteria

Inclusion Criteria	Exclusion Criteria
- Adults ≥18 years of age - WHO performance score of 0 or 1 - Cytologically or histologically confirmed diagnosis of stage IIIB/C/D/IVM1a (AJCC 8th edition) melanoma, eligible for surgical resection - Measurable disease according to RECIST 1.1 and must be a candidate for intralesional therapy with at least one injectable cutaneous, subcutaneous or nodal melanoma lesion (≥ 10 mm in longest diameter) or with multiple injectable lesions that in aggregate have a longest diameter of ≥10 mm - Prior isolated limb perfusion is allowed (≥ 12 weeks prior to enrollment) - **Adequate organ function** - LDH < 2 x ULN - INR or PT ≤1.5 x ULN, unless the subject is receiving anticoagulant therapy - WOCBP must use highly effective method(s) of contraception during T-VEC and nivolumab treatment and for a period of 5 months after the last dose of nivolumab - WOCBP must have a negative serum or urine pregnancy test within 72 hours prior to enrollment and within 24 hours prior to the start of nivolumab - Men receiving nivolumab and who are sexually active with WOCBP should use contraception during treatment and for a period of 7 months after the last dose of nivolumab - Men who are sexually active with WOCBP must use any contraceptive method with a failure rate of less than 1% per year - Women who are not of childbearing potential (i.e., who are postmenopausal), or surgically sterile as well as azoospermic men do not require contraception - Patient is capable of understanding and complying with the protocol requirements and has signed the Informed Consent document - Inhaled or topical steroids, and adrenal replacement steroid < 10 mg daily prednisone equivalent, are permitted in the absence of active autoimmune disease	- Liver, bone, lung, brain or other visceral metastases - Prior radiotherapy for melanoma - Prior systemic cancer therapies, including, but not limited to anti-CTLA-4, anti-PD-1, anti-PD-L1 - Other malignancies, except adequately treated and a cancer-related life-expectancy of more than 5 years - Positivity for hepatitis B virus surface antigen or hepatitis C virus ribonucleic acid, indicating acute or chronic infection - Known history of testing positive for HIV or known AIDS - History or evidence of active autoimmune disease that requires high dose systemic treatment. Replacement therapy is not considered a form of systemic treatment - Evidence of clinically significant immunosuppression such as a primary immunodeficiency, a concurrent opportunistic infection, receiving systemic immunosuppressive therapy (> 2 weeks) including oral steroid doses > 10 mg/day of prednisone or equivalent within 7 days prior to enrollment - Active herpetic skin lesions or prior complications of HSV-1 infection - Requirement of intermittent or chronic systemic (intravenous or oral) treatment with an antiherpetic drug, other than intermittent topical use - Previous treatment with T-VEC or any other oncolytic virus - Received live vaccine within 30 days prior to enrollment - Subject has known sensitivity to T-VEC or nivolumab or any of its components to be administered during dosing - Sexually active subjects and their partners unwilling to use male or female latex condom to avoid potential viral transmission during sexual contact while on treatment and within 30 days after treatment with T-VEC - Subjects who are unwilling to minimize exposure with his/her blood or other body fluids to individuals who are at higher risks for HSV-1 induced complications during T-VEC treatment and through 30 days after the last dose of T-VEC - No allergies and adverse drug reaction - History of allergy to study drug components or severe hypersensitivity reaction to any monoclonal antibody - No underlying medical conditions that, in the Investigator’s opinion, will make the administration of study drug hazardous or obscure the interpretation of toxicity determination or adverse events - Use of other investigational drugs before study drug administration 30 days and 5 half-times before study inclusion

*AIDS* acquired immunodeficiency syndrome; *AJCC* American Joint Committee on Cancer; ALT alanine aminotransferase; *AST* aspartate aminotransferase; *CTLA-4* Cytotoxic T-lymphocyte-associated protein-4; *HCG* human chorionic gonadotropin; *HIV* human immunodeficiency virus; *HSV-1* herpes simplex virus type − 1; *INR* international normalization ratio; *LDH* lactate dehydrogenase; *PD-1* programmed cell death protein-1; *PT* prothrombin time; *RECIST* Response Evaluation Criteria in Solid Tumors; *T-VEC* Talimogene laherparepvec; *ULN* upper limit of normal; *WHO* World Health Organization; *WOCBP* women of childbearing potential

### Study procedures and intervention

Prior to enrollment, all patients will be adequately informed by the investigator(s) about participation in the trial. Participation is voluntary and patients are allowed to withdraw from the trial at any time. Following signing of the informed consent form for screening and enrollment into the study, the remainder of the screening procedures and tests will be completed and evaluated before start of treatment. If the screening shows that patients do not fulfill the eligibility criteria anymore, patients will be withdrawn from the study and will be replaced by another patient. See Table 2 for the full schedule of screening assessments and study procedures.

**Table 2 Tab2:**
[figure not shown]
Schedule of enrollment, interventions and assessments

*And when clinically indicated. ^#^According to national/institute’s standards. ^1^Follow-up assessments according to local protocol/standard of care. Every 12 weeks (unless stated other) for up to two years after adjuvant treatment, year 3, 4, 5 according to institute’s standard. ^2^Clinical photographs will be taken of all cutaneous lesions, noting in detail the exact size and location of any (skin) lesions that exist. ^3^Hematology and chemistry. At screening, PT/INR, aPTT and serology (HIV, HbsAG, anti-HCV, HSV, anti-CMV) are also determined. ^4^Every 12 weeks during follow-up. ^5^T-VEC seroconversion dose 10^6^ PFU/mL. ^6^T-VEC dose 10^8^ PFU/mL. ^7^AEs will be graded according to CTCAE v5.0 from moment of signing informed consent. New occurring AEs and any SAEs will reported up to 100 days post last treatment. ^8^Only registration of medication that is used for treatment of immune-related AEs from moment of signing informed consent. ^9^Toxicity from prior treatment will be evaluated. ^10^100 ml heparinized blood (for PBMC). ^11^Only at week 3 prior to first nivolumab. ^12^At relapse. ^13^20 ml EDTA blood (for isolation of plasma for ctDNA). ^14^Three biopsies taken with a 14G needle of thru-cut and will be stored as fresh frozen and formalin-fixed paraffin-embedded material for translational research purposes. At baseline pathological confirmation of melanoma will be performed. ^15^If possible, surgical material should be preserved as fresh frozen and formalin-fixed paraffin-embedded material

*AE* adverse event; *aPTT* activated partial thromboplastin time; *CMV* Cytomegalovirus; *CT* computed tomography; *CTCAE* Common Terminology Criteria for Adverse Events; *ECG* electrocardiogram; *EDTA* Ethylenediaminetetraacetic acid; *HbsAG* hepatitis B virus surface antigen; *HCG* human chorionic gonadotropin; *HCV* hepatitis C virus; *HIV* human immunodeficiency virus; *HSV* herpes simplex virus; *INR* International normalization ratio; *MRI* magnetic resonance imaging; *PBMC* peripheral blood mononuclear cells; *PET* Positron Emission Tomography; *PFU* plaque-forming units; *PTT* partial thromboplastin time; *SAE* Serious Adverse Event; *WOCBP* women of childbearing potential

The total neoadjuvant treatment duration comprises 7 weeks and is followed by surgery in week nine. The treatment schedule is based on four courses of T-VEC and three courses of nivolumab:T-VEC: Up to 4 ml T-VEC (first dose 10^6^ plaque-forming units (PFU) per mL as a seroconversion dose, subsequent doses at 10^8^ PFU per mL) in week 0, 3, 5 and 7. The volume of T-VEC to be injected into the tumor depends on the size of the tumor(s) and will be determined based on the longest diameter of each lesion according to manufacturers’ protocol [27];Nivolumab: Flatdose of 240 mg nivolumab intravenously every 2 weeks after the first intralesional T-VEC injections (starting at the second T-VEC dose at week 3, followed by the next doses at week 5 and 7).

T-VEC will be administered first, in order to achieve the best synergistic effect with influx of CD8^+^ T cells [14]. Patients will be offered adjuvant treatment as standard of care following surgery. See Fig. 1 for a full overview of the course of the trial.

**Fig. 1 Fig1:**
[figure not shown]
Study Schedule. Blood draw for PBMCs will be performed at screening, week 3, week 9 (prior to surgery), and first evaluation (week 12) and at moment of relapse. Tumor biopsies will be taken at screening, prior to first nivolumab administration and at moment of relapse in all patients for translational research purposes. Biopsies will be preserved and stored as fresh frozen and formalin-fixed paraffin-embedded material at all indicated time points. *The first dose of T-VEC is a seroconversion dose. CT, computed tomography; LDH, lactate dehydrogenase; MRI, magnetic resonance imaging; PBMC, peripheral blood mononuclear cells; PET, Positron Emission Tomography; PFU, plaque-forming units; QoL, quality of life questionnaires; RECIST, Response evaluation criteria in solid tumors; T-VEC, Talimogene laherparepvec; ULN, upper limit of normal; WHO PS, World Health Organization performance status

### Evaluation and follow-up of participants

Prior to each treatment course, physical examination, laboratory analyses and evaluation of toxicity will be performed in each patient. Additionally, photos of cutaneous lesions will be taken. At baseline, before first nivolumab administration, time of surgery and moment of potential relapse, blood- and tumor samples will be collected for translational research purposes. Health-related quality of life assessment will be performed at baseline, prior to surgery, at week 12 and every follow-up.

Prior to surgery, patients will undergo physical examination, laboratory analyses and a Computed Tomography (CT) scan. Following surgery, patients will be evaluated every 12 weeks during the first 2 years after the end of adjuvant treatment by physical examination, laboratory analyses, CT or PET-CT (according to center's discretion). Subsequent structured follow-up will be according to the current national melanoma guidelines. In case of progression to unresectable stage III or stage IV melanoma, follow-up data will be collected until first systemic treatment dose. After initiation of systemic treatment, only the OS data will be collected. See Fig. 1 and Table 2 for all specific time points and study assessments.

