#### Exploratory endpoints

Response rate according to RECIST 1.1 at week eight;Quality of life as measured by EORTC QLQ-C30 and the Melanoma Surgery Subscale of the FACT-M.

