### Evaluation of health-related quality of life

Health-related quality of life will be assessed with the European Organization for Research and Treatment of Cancer Quality of Life Questionnaire Core 30 (EORTC QLQ-C30), a self-reported questionnaire specifically developed for patients with cancer who are receiving cancer treatment and is the most common quality of life instrument used in melanoma studies [30]. The guideline of Cocks et al. [31] will be used for the interpretation of changes in QLQ-C30 scores. Additionally, the Melanoma Surgery Subscale of the FACT-M [32] will be evaluated in all patients every 12 weeks during the first year and at year two and three.

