This dosing schedule will result in a short delay for patients compared to standard treatment, as regular times to surgery in The Netherlands are 4–6 weeks. However, standard of care for this patient population would be surgery followed by adjuvant ICI. In this trial, patients will already have received three courses of ICI in combination with T-VEC prior to surgery. Considering the very high chance of relapse in this patient category (approximately 70–80% risk) [33], any neoadjuvant approach might reduce this risk of relapse, adding to the chance of a more durable response for these patients, comparable to the observed results from the earlier neoadjuvant OpACIN and OpACIN-neo studies [21, 22]. Results from Dummer et al. [25], already demonstrated 25% less chance of recurrence in patients with resectable stage IIIB-IVM1a melanoma when treated with neoadjuvant T-VEC compared to surgery alone. For patients with subcutaneous or in-transit metastases, who are often excluded from ICI neoadjuvant trials [22] and who would otherwise receive locoregional management (followed by adjuvant therapy in case of surgery) or systemic therapy as standard of care, this neoadjuvant approach could be extra beneficial. Additionally, some patients may have the chance to undergo less extensive surgery, or no surgery at all, due to a good clinical response upon neoadjuvant treatment.

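### Quality-of-life collection ends when systemic treatment for advanced progression starts, which conflicts with the questionnaire schedule and leaves late results describing a selected group

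*Protocol article*

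**What the plan says.** Three statements in the protocol article bear on this point.

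- **Evaluation and follow-up of participants, schedule:** "Health-related quality of life assessment will be performed at baseline, prior to surgery, at week 12 and every follow-up".
- **Same section, next paragraph, stopping rule:** "In case of progression to unresectable stage III or stage IV melanoma, follow-up data will be collected until first systemic treatment dose". It continues: "After initiation of systemic treatment, only the OS data will be collected".
- **Evaluation of health-related quality of life:** the FACT-M Melanoma Surgery Subscale "will be evaluated in all patients every 12 weeks during the first year and at year two and three". No exception is named. For the other questionnaire, a published guideline "will be used for the interpretation of changes in QLQ-C30 scores".

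Quality of life is listed under Exploratory endpoints: "Quality of life as measured by EORTC QLQ-C30 and the Melanoma Surgery Subscale of the FACT-M". The article gives no hypothesis, summary measure or model for it.

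**The concern.** The stopping rule and the two schedules cannot all be followed as written. A patient with stage IV progression who starts systemic treatment in the second year is still due the surgery subscale at years two and three, but under the stopping rule only survival is recorded.

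If the stopping rule prevails, the reason for the missing data is the disease itself. The patients who leave the series are those with treated advanced progression, whose scores are the most likely to be worse. The trial has a single arm, so no comparison group suffers the same loss. A late result could then be read as quality of life preserved in the cohort when it describes only patients who have not reached that stage.

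The loss arises at collection. A later analysis plan can choose a model, but it cannot recover questionnaires that were never given. Any model would have to rest on untestable assumptions about patients who are unobserved by rule.

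**Working it through.** **Plan's own figure.** The article states no number for quality of life, so there is nothing to reproduce. Its power figures concern pathologic response and surgical success and do not enter here.

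**Inputs from the article**
- Sample size: 24.
- Stopping trigger: first systemic dose after unresectable stage III or stage IV progression.
- Relapse risk: about 70–80% (Discussion). It covers relapse generally, with no time horizon and no share for advanced disease treated systemically.

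**Inputs assumed (not in the article)**
- f, the share of patients due a late questionnaire whose collection has stopped: 20% to 60%.
- D, the late mean score of those still observed minus the late mean score the others would have had: 10 to 20 points on a 0–100 scale where higher is better.
- Deaths are set aside.

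**Step 1: gap between the observed late mean and the cohort's late mean**

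Cohort mean = (1 − f) × observed mean + f × unobserved mean, so

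observed mean − cohort mean = f × D.

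| f | Patients left, 24 × (1 − f) | Gap, D = 10 | Gap, D = 20 |
|---|---|---|---|
| 0.2 | 19.2 | 2 | 4 |
| 0.4 | 14.4 | 4 | 8 |
| 0.6 | 9.6 | 6 | 12 |

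The range is 2 to 12 points.

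**Step 2: does the observed series have to rise?**

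Let g be the baseline score of patients who stay minus that of patients who later leave. Let w be the mean within-patient change in those who stay. Comparing the late observed mean with the whole-cohort baseline mean gives

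apparent change = f × g + w.

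- g = 0, w = −3, any f: change = −3.
- g = 5, f = 0.4, w = −3: 0.4 × 5 − 3 = −1.
- g = 10, f = 0.4, w = 0: 0.4 × 10 + 0 = +4.

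The observed series can fall, stay flat or rise. The gap in step 1 does not determine its direction.

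**Step 3: what paired change does and does not repair**

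Let v be the mean change that the unobserved patients would have had. Then D = g + (w − v), and

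f × D = f × g + f × (w − v).

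Pairing each contributor with their own baseline removes f × g. It leaves f × (w − v). Take f = 0.4, g = 5, w = −3, v = −8, so D = 5 + 5 = 10:

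- true cohort change: 0.6 × (−3) + 0.4 × (−8) = −5;
- raw means: −1, too favourable by 4;
- paired change in contributors: −3, too favourable by 2 for the cohort, but correct for the contributors.

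Paired change is therefore an accurate statement about a narrower group. Only continued collection gives the cohort result.

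**The case against.** **Quality of life is exploratory, and stopping at the next line of treatment is a coherent choice,** because later scores also reflect that treatment. This stands as to importance. It does not remove the conflict: if this is the choice, the schedule should say so and the results should be labelled accordingly.

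**The article plans no yearly means and no trend.** This is correct. It says only that changes in QLQ-C30 scores will be interpreted, which is compatible with within-patient change, and the analysis detail may properly sit in a plan not shown. A reader might infer that scores will improve over time by construction. The documents do not support that: no such series is planned, and step 2 shows that the direction is not fixed.

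**The size is all assumption.** This also stands. A reader might take the 70–80% relapse risk as the share lost. It is not: patients with resectable relapse fall outside the stopping rule, and patients with advanced progression contribute until their first systemic dose. Nor is standard adjuvant treatment most naturally the trigger, since the sentence follows on from progression.

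**The literal reading may not be intended.** The quality-of-life section may be meant to override the stopping rule, and the grid of Table 2 and Fig. 1, which I could not see, may settle it. That is a reason to reconcile the text; as it stands, the wording restricts collection to survival.

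**Early data may not be complete either.** A reader might assume that every patient contributes up to week 12. The stopping rule has no lower time limit. Both the event-free survival definition and the Statistical considerations section foresee progression that prevents surgery, so a patient could start systemic treatment before week 12.

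**Conclusion.** The point holds as a minor one. The article contradicts itself on whether questionnaires continue after systemic treatment for advanced progression starts. If they stop, late data are missing for reasons tied to outcome, and late summaries describe patients who have not reached that stage.

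Such summaries are probably too favourable for the whole cohort, provided that the patients who stop would have scored worse. That is plausible but not shown by the article. The size is unknown: 2 to 12 points illustrates f × D for assumed losses of 20% to 60% and assumed differences of 10 to 20 points. It is not an estimate for this trial.

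The documents do not support saying that quality of life will appear to improve. They support saying that late results cannot be read as results for all 24 patients. No primary or secondary conclusion is affected.

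**What to change.** Reconcile the stopping rule in Evaluation and follow-up of participants with the every-follow-up schedule in that section and with the all-patient schedule to year three in Evaluation of health-related quality of life.

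1. **Preferred:** state that the QLQ-C30 and the surgery subscale continue at their scheduled times after systemic treatment for progression starts. The cost is a few added questionnaires in patients already followed for survival. At the reported status (13 of 24 enrolled on 31 May 2022), 11 patients were still to be enrolled.
2. **Otherwise:** keep the stopping rule, remove the conflicting wording, and label late results as quality of life before systemic treatment for advanced progression. Report the number contributing at each visit, including before surgery and at week 12, and the paired change against those same patients' baseline. This needs only wording. The cost is a narrower long-term claim, and, as step 3 shows, it does not recover the cohort result.
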